# 6 Study Intervention

## 6.1 Study Intervention(s) Administration

### 6.1.1 Study Intervention Description

The intervention will not interfere with or supersede standard ED care for post-tonsillectomy hemorrhage. After determination of eligibility and obtaining informed consent, patients will be randomized to receive nebulized TXA or saline. The only change to ED PTH management is the addition of nebulized study drug. This randomized pilot trial will thus evaluate the feasibility to enroll patients into a trial that will determine the efficacy of nebulized TXA (investigational drug) compared to nebulized normal saline (placebo) to prevent repeat surgical intervention.

### 6.1.2 Dosing and Administration

The investigational product, TXA 100 mg/mL, is approved in a pediatric population for treatment of hemorrhage post-tooth extraction, and for short-term treatment of hemophilia. For this study, nebulized TXA will be administered in a double-blinded randomized protocol to children who are 2 to 17 years of age, using nebulized saline as a placebo. The study interventions should not interfere with standard of care. is not needed, the clinical nurses or respiratory therapists can administer a study medication per protocol, after receiving protocol training.

## 6.2 Preparation/Handling/Storage/Accountability

### 6.2.1 Acquisition and accountability

The study drug will be purchased or supplied by American Regent (generic version of the injectable 100 mg/mL) in bulk as 0517-0960-10 × 10 mL single dose vial. The placebo (0.9% sodium chloride, NDC 0517-2810-25 x 10 mL single dose vial) will be purchased from a similar manufacturer and then repackaged by a Hybrid Pharma, [name], [[contact]](mailto:[contact]), Ph: [name], [contact] into identical vials that TXA originally is packaged in. Study drugs will be received by a hospital investigational pharmacist, who will prepare “Use Next Boxes” for the ED.

The nebulizer mask used to deliver the TXA will be provided with the study drug as the PARI LC® D Disposable Nebulizer (PARI Respiratory Equipment, Inc., Midlothian, VA) or a similar jet nebulizer based on supplies.

### 6.2.2 Formulation, Appearance, Packaging, and Labeling

Study drug and saline will come in similar vials, as described above, that can be blinded by placing a label over the original packaging.   The pharmacist will blind (please see example in Figure 4) two vials of study drug or placebo assigned per randomization schedule. Then they will be placed in the "Use Next Box" for the randomization and dosing process.

[figure not shown]

**Figure 4: Study Drug Investigational Drug Labelling.**

### 6.2.3 Product Storage and Stability

For TXA and saline: Store at 20°C-25°C (68°F-77°F); excursions permitted from (59°F-86°F) [see USP Controlled Room Temperature].

### 6.2.4 Preparation

Upon enrollment into the study, clinical staff will load the study drug into a nebulizer well (PARI LC® D Disposable) and then deliver the TXA or placebo via a mask. Study drug will be nebulized using the hospital gas supply. All personnel except the investigational pharmacist and/or statistician will be blinded to the drug. The randomization schedule will be pre-determined by a central randomization process and prepared as "Use Next boxes" to decrease the need for the randomization process at enrollment.  "Use Next Boxes" will have three study drug doses (blinded by an investigational pharmacist), a study nebulizer, and instructions for study drug delivery.

## 6.3 Measures to Minimize Bias: Randomization and Blinding

Due to the narrow time window of study intervention, randomization must not delay treatment. To complete the randomization quickly, the study intervention will be preassigned using a central randomization process. Prior to enrollment at each site, a study drug box having two vials (1000 mg per vial) of blinded study drug with a numeric identification code corresponding to the treatment assignment will be designated as the “Use Next Box." All interventions will be blinded to the investigator, clinical care team, and research staff. Only the pharmacist and biostatistician will know the randomization schedule. Unblinding is not allowed. Clinicians will be instructed to assume that the patient has received TXA and treat accordingly.

## 6.4 Study Intervention Compliance

Every week of the study enrollment, study staff will review and complete data entry for patients screened or missed eligible patients. All relevant surgical and clinical data will be collected related to risk factors for PTH, pharmacokinetics, or receipt of study drug or placebo (please see the schedule of activities). Relevant data collection for enrolled PTH patients includes BMI, historical platelet counts, episodes of bleeding or clotting, insurance, ethnicity, surgical tonsillectomy technique performed, prescribed and over the counter medications, and other data as will be described in the manual of operations. Data collected on missed eligible patients, using a waiver of consent, will be age, sex, height, and weight if available, medications taken upon admission, insurance, and outcomes including surgery performed or not. For more details see the Manual of Operations. Data will be collected and managed using REDCap hosted at the University of Utah. REDCap (Research Electronic Data Capture) is a secure, web-based application designed to support data capture for research studies. Below is a table of associate responsibilities.

| **Procedure** | **Data Source** | **Responsible** |
| --- | --- | --- |
| Screening and eligibility | Electronic Health Record (EHR) | Research Staff* |
| Medical History | EHR or study staff | Clinical and Research Staff |
| Consent | E-consent, Virtual, or in Person | Research Staff |
| Demographics/baseline information | EHR or study staff | Clinical and Research Staff |
| Concomitant medication review | EHR | Clinical and Research Staff |
| ED/Hospital admission data collection | EHR | Clinical and Research Staff |
| Administer study nebulization 1 | EHR or study staff | Clinical and Research Staff |
| Administer study nebulization 2 | EHR or study staff | Clinical and Research Staff |
| Administer study nebulization 3 | EHR or study staff | Clinical and Research Staff |
| Surgical Hemorrhage Control? (Y/N) | EHR or study staff | Research Staff |
| 1st TXA Level (last neb up to 60 mins) | Blood Sample | Clinical and Research Staff |
| 2nd TXA Level (60 mins to 8 hours) | Blood Sample | Clinical and Research Staff |
| Process, Freeze, Store and Ship | Plasma Samples | Research Staff |
| ENT Surgical Decision Survey | ENT Surgeon | Research Staff |
| Age-Appropriate Pain Scale | EHR, Text, or Phone | Research Staff |
| Promis Anxiety Scale (Parent and Child) | EHR, Text, Phone, or Virtual | Research Staff |
| Adverse Events/UPIRSO | Text, Phone, Virtual | Research Staff |
| Serious Adverse Events | Text, Phone, Virtual | Research Staff |
| Missed Eligible | EHR | Research Staff |

* Research staff can refer to research coordinators, co-investigators, principal investigator, or other study team members who have been trained to be part of the study

## 6.5 Concomitant Therapy

TXA has very few if any drug metabolism interactions. Patients will be allowed to take over-the-counter medications for pain that affect bleeding (e.g., non-steroidal anti-inflammatory drug), birth control (estrogen-containing products), or retinol A. Records of all doses and frequency of these medications will be collected during the perioperative course through retrospective chart review.

### 6.5.1 Rescue Medicine

There is no rescue medication for the study drug (TXA or placebo). If there is an allergic reaction, the study drug will be stopped, and routine care for allergic reactions will be followed.

# 7 Study Intervention Discontinuation and Participant Discontinuation/Withdrawal

## 7.1 Discontinuation of Study Intervention

Study drug or placebo administration will be discontinued if the patient experiences any allergic or anaphylaxis reaction. If a severe anaphylactic reaction or severe vomiting occur during or after administration, clinical staff and study team should assume the patient received a study drug as there will be no unblinding procedures.

Discontinuation from study drugs does not mean discontinuation from the study, and remaining study procedures should be completed as indicated by the study protocol.  If a clinically significant finding is identified (including but not limited to changes from baseline) after enrollment, the investigator or qualified designee will determine if any change in participant management is needed. Any new clinically relevant finding will be reported as an adverse event (AE). The data to be collected at the time of study intervention discontinuation will include the following pharmacokinetic studies and clinical case report forms as indicated above.

## 7.2 Participant Discontinuation/Withdrawal from the Study

Participants are free to withdraw from participation in the study at any time upon request. A site investigator may discontinue or withdraw a participant from the study for the following reasons:

1. If any clinical adverse event (AE), laboratory abnormality, or other medical condition or situation occurs such that continued participation in the study would not be in the best interest of the participant.
2. Emergent intubation for respiratory failure.
3. If the participant meets an exclusion criterion (either newly developed or not previously recognized) that precludes further study participation.

The reason for participant discontinuation or withdrawal from the study will be recorded on the Adverse Event Case Report Form. Subjects who sign the informed consent form and are randomized but do not receive the study intervention may be replaced.  Subjects who sign the informed consent form, are randomized, and receive the study intervention, and later withdraw or are discontinued from the study, will no longer have data collected, but existing data collected prior to withdrawal will still be used. Subjects may be replaced as necessary depending about withdrawal.

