# 1 Protocol Summary

## 1.1 Synopsis

| **Title:** | TranExamic Atomized for Pediatric post-Operative Tonsillectomy hemorrhage: A Pilot and Feasiblity Study |  |  |  |
| --- | --- | --- | --- | --- |
| **Study Description:** | This study starts as single site pilot study, randomized, double-blinded controlled trial for 12 patients. Then dependent on funding, the study will be a multi-center, randomized, double-blinded, placebo-controlled trial. It is a parallel arms pilot trial randomizing up to 30 patients. |  |  |  |
| **Objectives:** | \| Primary Objective: \| The primary objectives of this pilot study are:   1. Enroll 0.6 patient's/site/month with PTH and 2. Evaluate the ability to nebulize at least two doses of TXA to children with PTH and 3. Determine the indirect local and systematic concentrations of nebulized TXA in children 4. Adverse events will be assessed 30 +/- 5 days from randomization \| \| \| \| --- \| --- \| --- \| --- \| \| Secondary Objectives: \| The secondary objectives of this pilot study are:   1. Determine the number and rationale for PTH patients to return to the OR; and 2. Determine the number of blood transfusions and estimated blood loss and 3. Determine the recurrence of PTH after TXA, saline or return to the OR. \| \| \| \| Exploratory Objectives: \| \| Establish pain and anxiety inventory at 7 +/- 1 from randomization. \| | | |  |
| **Endpoints:** | \| Primary Endpoint: \| Enrollment after one year, % of nebulization administered to patient's enrolled, and collection of two blood samples from each participant. Adverse events will be assessed at 30 +/- 5 days from randomization. \| \| --- \| --- \| \| Secondary Endpoints: \| Collection of surveys on ENT decision to go to the OR, electronic health record data on blood transfusions and estimated blood loss, and if PTH recurrences within seven days of randomization. \| \| Exploratory Endpoints: \| Age-appropriate pain and anxiety states at 7 +/- 1 days after randomization. \| | | | |
| **Study Population:** | Children aged 2 to 17 years old that present with post-tonsillectomy hemorrhage (PTH), ENT clinicians, parents of the children enrolled and missed eligible. | |  |  |
| **Phase:** | 2 | |  |  |

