# 3 Objectives and Endpoints

| OBJECTIVES | ENDPOINTS | JUSTIFICATION FOR ENDPOINTS |
| --- | --- | --- |
| Primary | | |
| Evaluate the feasibility to enroll 0.6 patients/site/month  Nebulize at least two of three doses of TXA to children with PTH.  Determine the local and systematic concentrations of nebulized TXA in children  Determine incidence of adverse and serious adverse events | Enrollment after one year and % of nebulization’s. Go/no-go threshold is 0.6 patients per site per month for a total of 22 patients. Time and success to obtain consent will establish need for exception for informed consent (EFIC).    The goal is >90% of patients will receive at least two of three planned nebulization of TXA.  Collection of two blood samples from each participant. This will verify a pulmonary physiological-based PK model (PBPK) (i.e., nasal cavity, pharynx, and lung) that indirectly predicts the oropharyngeal and systematic concentration of nebulized TXA.  A phone call or email will be placed to participants at 30 +/- 5 days. | The overall incidence of PTH is 5%, yet numbers per site may be very different. Assessment and consent will optimize site selection, recruitment process, and the plan the main trial.    The establishment of a pragmatic protocol design will help design a large trial.  Limited data on nebulized TXA systematic absorption. Topical PK studies of TXA document a significant reduction in systematic levels but the same hemostasis effect.  Safety Evaluation as recommended by the FDA. |
| Secondary | | |
| Determine the number and rationale for PTH patients to return to the OR; and    Determine the number of blood transfusions and estimated blood loss and      Determine the recurrence of PTH after TXA, saline, or return to the OR. | Collection number participants and surveys on ENT surgeons’ decision to go to the OR    Collection of electronic health record data on number of blood transfusions and estimated blood loss    Survey families to determine PTH recurred seven days from randomization. | To evaluate if return to the OR can be an outcome for the main trial.    To evaluate if TXA decreased severity of PTH bleeding.      To evaluate if TXA or return to OR prevented PTH recurrence. |
| Tertiary/Exploratory | | |

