# 8 Study Assessments and Procedures

## 8.1 Efficacy Assessments

The **primary feasibility outcomes** for the pilot trial are the enrollment rate (patients per site per month) and the proportion of patients receiving study drugs (at least 2 nebulized doses).  Safety is always an outcome, and all adverse events will be reviewed.

**The secondary outcome is** the ENT surgeon rationale, decision (Y/N) for the PTH patient to return to the OR, severity of bleeding with estimates of blood loss that include volume of hemorrhage recorded blood loss, and the number of blood transfusions. Additionally, we will determine the indirect local and systematic concentration of nebulized TXA by verifying our pulmonary physiologically based pharmacokinetic model. To verify the model, two lab samples will collect at opportunistic times either by finger stick or ad**. The study is not** powered for the secondary outcomes as this a pilot trial.

The **exploratory outcomes** will be age-appropriate pain scores and parent and child anxiety scales as measured by anxiety-state-trait scale (STAI). For children under eight years old their anxiety will be measured by STAI-C, which utilized pictures These will be exploratory as the pilot trial is not powered to determine the change in the outcomes.  Please see **Figure 7** for a timeline of all study procedures and outcomes.

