# 9 Statistical Considerations

## 9.1 Statistical Hypotheses

The pilot study is not designed to test an efficacy hypothesis, but rather to determine the feasibility for patient enrollment and the number of doses received per patient.

**Our primary hypothesis** for the single site and the multi-site study is that we can enroll at least 0.6 patients per site per month and deliver a minimum of two out of three planned nebulized TXA doses to >90% of enrolled patients.  The single site study will only be one year and the multi-site study for 18 months. We will test each of this (yes/no) hypothesis using a Mantel Haenszel test stratified by site for a total of 12 patients for the single-site study for greater than 24 nebulization and for the multi-site study up to 22 patients with greater than 44 nebulization's recorded as delivered.

**Our secondary goals** will be to determine if nebulized TXA prevents going to the OR for PTH and utilization of blood products. These goals are not powered to be tested in the pilot study. **Our second aim** is to verify a pulmonary physiological based pharmacokinetic (PBPK) model (i.e., nasal cavity, pharynx, and lungs) will predict the change in the area under the curve (AUC0-α) of TXA concentration in systemic compartments with accuracy (average absolute fold error <2) and precision (average fold error <2). We will calculate the AUC of accuracy and precision of the model using the linear trapezoid rule. For the PBPK model, we will use previously published PK data to construct the model before verifying it with systematic samples.

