## 9.3 Populations for Analyses

A. Received nebulized TXA

B. Received nebulized saline (placebo control)

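### The as-treated populations in 9.3 and the replacement rule in 7.2 conflict with the enrolled-patient denominator of the >90% delivery hypothesis, so children who receive no dose can drop out of it

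*Protocol*

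**What the plan says.** **Delivery endpoint.** Protocol 9.1 gives the primary hypothesis for delivery as "deliver a minimum of two out of three planned nebulized TXA doses to >90% of enrolled patients". The synopsis (1.1) likewise describes the endpoint as a percentage "of nebulization administered to patient's enrolled". Two other places leave the denominator open. Section 3 states: "The goal is >90% of patients will receive at least two of three planned nebulization of TXA". Section 8.1 refers to "the proportion of patients receiving study drugs (at least 2 nebulized doses".

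**Timing.** Under 4.1, randomisation takes place at consent in the emergency department, before the first nebulization. A child can therefore be enrolled and randomised and still receive nothing.

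**Populations.** Section 9.3 consists of two entries: "A. Received nebulized TXA" and "B. Received nebulized saline (placebo control". It names no enrolled or randomised set.

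**Replacement.** Section 7.2 says: "Subjects who sign the informed consent form and are randomized but do not receive the study intervention may be replaced". It adds an open-ended rule: "Subjects may be replaced as necessary depending about withdrawal". For treated children who later withdraw, it says that data already collected will be used. For randomised, undosed children it does not say whether they still count.

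**The concern.** The hypothesis in 9.1 needs a denominator that 9.3 does not supply and that 7.2 allows to be refilled with dosed children. An analyst who follows 9.3 to the letter will compute delivery among children who received at least one nebulization. The children left out are the plainest delivery failures, for example a child taken to surgery or intubated before the first dose. The protocol makes such cases plausible: it puts the share of these children who go to the OR at 76% (9.2), says that the study must not interfere with standard ED care (6.1.1), and lists emergent intubation as a reason for withdrawal (7.2).

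The delivery percentage is meant to show whether the dosing protocol is practicable for a larger trial, so removing these children inflates the quantity that the pilot is there to measure. Return to the OR may be affected as well. Section 9.4.2 compares the arms on it, and section 3 wants it assessed as a possible outcome for the main trial. If children who went to surgery undosed are left out, that rate is misestimated.

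**Working it through.** **Inputs from the protocol**
- Targets: 12 patients at the single site and 22 in the multi-site study (9.1, 9.2).
- Success for a child: at least two of three nebulizations. Goal: more than 90% of children (9.1).
- Number randomised but never dosed: not stated. Write it as k; every value of k below is an assumption.

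**The plan's own figures**
- Multi-site target: 0.6 × 3 sites × 12 months = 21.6, rounded up to 22. Reproduced.
- Nebulization counts: 12 × 2 = 24 and 22 × 2 = 44. Reproduced. They also show that delivery is counted over all patients, not over the TXA arm alone.

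**Smallest passing result**
- n = 12: 10/12 = 83.3% fails and 11/12 = 91.7% passes.
- n = 22: 19/22 = 86.4% fails and 20/22 = 90.9% passes.

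**Effect of the denominator**

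Let n be the number of treated children after replacement and s the number with at least two doses. The 9.3 populations give s/n. All randomised children give s/(n + k). A zero-dose child is never in s, so only the denominator changes.

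| Scenario | s/n | k = 1 | k = 2 | k = 3 |
|---|---|---|---|---|
| Single site, just passes | 11/12 = 91.7% | 11/13 = 84.6% | 11/14 = 78.6% | 11/15 = 73.3% |
| Single site, all treated succeed | 12/12 = 100% | 12/13 = 92.3% | 12/14 = 85.7% | 12/15 = 80.0% |
| Multi-site, just passes | 20/22 = 90.9% | 20/23 = 87.0% | 20/24 = 83.3% | 20/25 = 80.0% |
| Multi-site, all treated succeed | 22/22 = 100% | 22/23 = 95.7% | 22/24 = 91.7% | 22/25 = 88.0% |

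**Chance of observing more than 90%, under one assumed setting**

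Suppose that 10% of randomised children receive no dose and 5% receive exactly one. True delivery among all randomised is 1 − 0.10 − 0.05 = 85%. Among treated children it is 0.85/0.90 = 94.4%. The binomial chances of a passing result (at least 11 of 12, or at least 20 of 22) are:
- All randomised: 44% (n = 12) and 34% (n = 22).
- Treated only, refilled to the same n: 86% and 88%.

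If 10% receive no dose and 10% exactly one, delivery among treated children is 0.80/0.90 = 88.9%, and the treated-only chances are 61% and 55%. Using treated children raises the chance of passing but does not make it certain.

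**The case against.** The strongest reply is that the protocol already has the right denominator. Section 9.1 and the synopsis say enrolled, and since randomisation comes at consent, that word naturally covers a child who then receives nothing. Replacement is permitted, not required, and adding a child does not in itself delete the one replaced. The pilot is analysed descriptively (9.4.1), and detail on analysis sets is often left to a statistical analysis plan.

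Much of this stands. A reader might infer that delivery is fixed to treated children and so biased by construction; the text does not settle that. A reader might also infer that delivery would be measured only where it had already succeeded. That is wrong even under 9.3, because a child with one dose is in the population and still counts as a failure. Nor do the documents support the inference that a no-go could become a go: sections 3 and 9.2 attach the go/no-go threshold to the enrolment rate alone, and the 90% figure is a goal within the primary hypothesis.

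What the reply does not remove is the conflict. The protocol does not simply leave populations to a later document. It lists them, and the list has no place for a child whom 9.1 counts. Section 7.2 does not say on which side a replaced child falls.

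**Conclusion.** The protocol contradicts itself on the denominator of the delivery endpoint, and this should be fixed. Applied as written, 9.3 together with replacement drops zero-dose children from the denominator and overstates delivery. The return-to-OR rate may also be misestimated; the direction depends on why those children went undosed.

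The size rests on an unstated zero-dose rate. One replaced child changes the conclusion only if the treated set barely passes. If every treated child succeeds, two are needed at the single site and three in the multi-site study. The effect is on the delivery half of the primary hypothesis, not on the enrolment threshold. With 12 or 22 children, one to three undosed children are enough to decide the result, so the rule should be settled before data are seen.

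**What to change.** 1. In 9.3, add a population of all randomised children by assigned arm. Use it for dose delivery and return to the OR, with zero doses counted as a delivery failure.
2. Keep the treated populations in 9.3 for safety and pharmacokinetics.
3. In 7.2, state that a replaced child stays in the all-randomised denominator, and that the number replaced will be reported.
4. Use the same denominator wording in sections 1.1, 3, 8.1 and 9.1.

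Replacement itself need not be restricted. Tying it to completion of the pharmacokinetic set, for instance, would require knowing which lost children were on TXA, which sits badly with the blinding in 6.3.

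The cost is a few sentences. Delivery needs no new data, since randomisation and each nebulization are already recorded. The delivery percentage may be less favourable, and return to the OR may be missing for undosed children who withdraw; that number should be reported too.
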